### General training principles

A sheet of ‘Exercise Safety Guidelines’ is provided to each intervention group participant. In order to maximize training effect and safety, participants are advised to hydrate well before, during, and after the exercise sessions. They should not exercise on an empty stomach or just after a big meal. It is recommended to participants to wear comfortable, well-fitted clothes, and non-slippery shoes. Participants initially start exercising at an easy level to become familiar with training and technology use. For safety reasons participants should have a chair placed to each side when exercising. Participants are advised to stop exercising and immediately consult their doctor if they feel unwell (i.e., due to a temporary illness, not taking their regular prescribed medications, having signs of angina pectoris; having difficulty breathing; and/or feeling dizzy, lightheaded or faint).

### Training content

#### Balance exercises

The principles of balance exercises are based on the Otago Exercise Program
[19,20] and the Weight-bearing Exercise for Better Balance (WEBB) program (
http://www.webb.org.au). The iStoppFalls program aims to improve static balance, leaning balance and stepping ability by practicing activities relevant to ADL. Three balance exergames were specifically developed for the iStoppFalls project ‘Bumble Bee Park’, ‘Hills & Skills’, and ‘Balance Bistro’ (Figure 
3). All games target motor skills related to postural control including walking, weight shifting, knee bending, and/or stepping in different directions. Additionally, cognitive tasks are added once participants reach higher exergame levels (dual-tasking). In the cognitive tasks, users have to identify, memorize, and remember items, or perform mathematical calculations which randomly appear on screen. Progression of balance exergames is achieved by reducing upper limb support (from two chairs to one chair to none), narrowing the base of support, adjusting speed of movement, increasing gaming duration, and proceeding to a higher difficulty level. Proceeding to a higher level depends on a participant's high score calculated as the sum of points of the different tasks (i.e., passed gates, collected fruits, memorized items). The users will get direct (real-time) feedback about their progress by duration, score, and progress information (i.e., time, missed gates, correctly identified items) displayed on the screen.

**Figure 3 F3:**
[figure not shown]
**Exergames for balance. (A)** ‘Bumble Bee Park’: walking on the spot avoiding approaching bumble bees, **(B)** ‘Hills n’Skills’: downhill skiing aiming for the gates, **(C)** ‘Balance Bistro’: stepping to the side collecting fruits.

#### Muscle strength exercises

The Ambient Assisted Exercise Program (AAEP) for iStoppFalls is based on the strength exercise component of the Otago exercise program
[19]. It incorporates exercises for muscle strength of the lower extremities used in ADL and balance recovery: knee extension, knee flexion, hip abduction, calf raises, and toe raises. For muscle strength training, 2 to 3 sets of 10 to 15 repetitions and rest periods of 2 min will be recommended. To ensure technically correct movements and maximal range of motion all users will be provided with visual and verbal instructions. Progression is achieved by increasing the number of repetitions, the number of sets, and the difficulty level (e.g., by using the provided ankle cuff weights ranging from 1 kg to 3 kg). Participants will reach the next level if they correctly perform 3 sessions. Users will get direct (real-time) feedback about their progress by duration, number of repetitions, adequacy of movements, and progress information (e.g., percentage of completed task) displayed on the screen (Figure 
4).

**Figure 4 F4:**
[figure not shown]
Strength exercises for (A) hip abduction muscles and (B) back knee flexor muscles.

#### Education material

The educational booklet contains information about fall prevention, exercise, healthy eating, general health, footwear, medication, environmental hazards, and emergency procedures. It also includes a home safety checklist and a fall quiz. This content is based on well-known risk factors for falls, evidence-based fall prevention interventions, and guided by good practice principles
[21]. The educational booklet aims to promote self-management, and offers simple and effective strategies to reduce fall risk.

#### Outcome measures

Participants will be assessed at baseline (0 weeks), in the middle (8 weeks), and at the end of the intervention period (16 weeks). The assessments will be conducted under standardized conditions at the study centres or in rooms provided by the retirement villages. Table 
1 outlines the assessments performed at different time points. Each assessment will take about two hours to complete. When a stopwatch is used, time will be recorded to the nearest 0.01 s. For the Timed Up and Go (TUG), walking, and sensor-based assessments, participants will be wearing a SMM device as a necklace at the height of the sternum.

**Table 1 T1:** Study assessments by time point

**Type of assessment**		**Outcome variable**	**Baseline assessments (week 0)**	**Re-assessments (week 8)**	**Post-assessments (week 16)**
Health	Demographics, health status, falls history	NA	X		
	12-item WHODAS 2.0	Secondary	X		X
	European Quality of Life – 5 Dimensions	Primary	X	X	X
	Iconographical – Falls Efficacy Scale	Secondary	X	X	X
	Falls and exercise adherence calendars	Secondary		Monthly	
Technical	Technology use	Secondary	X		
	SUS & PACES	Secondary		X	
	TAM & UTAUT	Secondary			X
	AttrakDiff2 & AFSS & DART	Secondary			X
Physical	Physiological Profile Assessment	Primary	X		X
	Short Physical Performance Battery	Secondary	X		X
	Sensor-based balance tests	Secondary	X	X	X
	Sensor-based reaction time tests	Secondary	X	X	X
	Sensor-based chair stand test	Secondary	X	X	X
	Timed Up and Go test	Secondary	X		X
	Steady-state walking speed (single and dual task)	Secondary	X		X
	Hand grip strength	Secondary	X		X
	IPEQ or PAQ-50+	Secondary	X	X	X
Cognition	Mini-Cog	NA	X		
	Addenbrooke’s Cognitive Examination III	Secondary	X		X
	Trail Making Test	Secondary	X		X
	Victoria Stroop test	Secondary	X		X
	Digit Symbol Coding test	Secondary	X		X
	Digit Span Backward	Secondary	X		X
	Attention Network Test	Secondary	X		X
	Counting backwards by three	Secondary	X		X
iStoppFalls system	Exercise adherence	Secondary		Continuously	
	User activity (i.e., set top box, tablet)	Secondary		Continuously	
Kinect sensor	Range of motion	Secondary	While exercising		
	21 Joint angles	Secondary	While exercising		
SMM sensor	Walking distance (m)	Secondary		Daily	
	Peak power sit-to-stand transfers (W)	Secondary		Daily	

AFSS = Activity Flow State Scale; DART = Dynamic Acceptance Model for the Re-evaluation of Technologies; IPEQ = Incidental and Planned Activity Questionnaire; NA = non-applicable; PACES = Physical Activity Enjoyment Scale; PAQ-50+ = Physical Activity Questionnaire for the population aged 50 years and older; SMM = Senior Mobility Monitor; SUS = System Usability Scale; TAM = Technology Acceptance Model; UTAUT = Theory of Acceptance and Use of Technology; WHODAS = World Health Organization Disability Assessment Schedule.

#### Demographic and general health

Participants will be sent a self-report questionnaire by post and will be requested to complete it prior to the baseline assessment. We will collect information on socio-demographic characteristics (age, gender, marital status, ethnicity, housing situation, economic status, previous occupation, education) and medical history (presence of medical conditions, medication use, history of falls). In addition, the following outcome measures will be assessed at baseline and 16 weeks follow-up.

The 12-item World Health Organization Disability Assessment Schedule (WHODAS) 2.0 is a generic assessment instrument for six domains of general health: understanding and communicating, mobility, self-care, interpersonal interactions, household and work activities, and participation in society (
http://www.who.int/classifications/icf/whodasii/en/). This self-administered questionnaire is short, simple, and easy to administer. It produces standardized disability levels and profiles linked to the International Classification of Functioning, Disability and Health (ICF)
[22].

The Patient Health Questionnaire (PHQ-9) is a 9-item questionnaire for screening, diagnosing, monitoring, and measuring the severity of depression
[23]. Each item is scored from 0 (not at all) to 3 (nearly every day) leading to the diagnosis of minimal (0 to 4 points), mild (5 to 9 points), moderate (10 to 14 points), moderately severe (15 to 19 points), and severe (20 to 27 points) depression. The PHQ-9 showed excellent internal reliability (Cronbach’s alpha = 0.86) and discriminant validity (area under the curve = 0.95)
[23].

The European Quality of Life – 5 Dimensions (EQ-5D-5-L) questionnaire was developed to generate a basic health index (
http://www.euroqol.org/eq-5d-products/eq-5d-5l.html). Participants will describe their health status in five dimensions: mobility, self-care, usual activities, pain/discomfort, and anxiety/depression. Each dimension has three possible levels: (i) no problem, (ii) moderate problems, or (iii) extreme problems. Thus, 243 health states represented by a 5-digit combination can be defined according to the relevant level within each dimension (e.g., 11111 represents no problems on any dimension). In addition, participants will report their overall health during the past 30 days on a continuous scale (0 to 100, higher score equals better health perception)
[24].

The Iconographical – Falls Efficacy Scale (Icon-FES) is an innovative way of assessing concern about falling
[25]. As part of the baseline assessments, the Icon-FES will be used to investigate the participants’ concerns about falling (
http://www.neura.edu.au/apps/iconfes). Thirty pictures of daily activities, each within a specific environmental context associated with different probabilities about falling (i.e., taking the escalator, going downstairs), will be graded by the participant on a 4-point Likert scale (1 = not at all concerned, 4 = very concerned). The Icon-FES has excellent psychometric properties and shows close continuity with the Falls Efficacy Scale International (Spearman’s rho = 0.742, P < .001)
[25,26].

#### Physical and functional assessments

The Physiological Profile Assessment (PPA) short version will be applied to generate an overall fall risk score based on tests which directly assess sensorimotor abilities: contrast sensitivity (Melbourne edge test (MET), peripheral sensation (proprioception), balance (sway when standing on medium-density foam with eyes open), lower extremity muscle strength (knee extension), and hand reaction time
[27]. In multivariate models these variables provide an overall falls risk score, and can predict those at risk of falling with 75% accuracy in community and retirement village settings. A PPA score indicates mild (<1), moderate (1–2), and marked (≥2) fall risk in relation to a normative database. In addition, two PPA long version tests for leaning balance will be applied (coordinated stability test and maximal balance range test).

The Short Physical Performance Battery (SPPB) will be used to assess lower extremity function based on the following tests: static balance (side-by-side, semi-tandem, and tandem stance), walking speed over 4 m (at normal pace), and the five times chair stand test
[28]. Each test will be assigned a score from 1 (worst) to 4 (best). Summing the category scores for the three tests can be used to create a SPPB summary performance scale.

The TUG by Podsiadlo and Richardson
[29] will assess a combination of basic functionality, physical mobility, and dynamic balance
[30,31]. On the word ‘go’, participants will have to stand up from a chair, walk to a three meter mark, come back, and sit down in the chair again. Time will be recorded with a stopwatch from the word ‘go’ until the participant sits down. Test-retest reliability of the TUG in older people is excellent (ICC = 0.99)
[29].

Steady-state walking speed will be measured over a 10 m distance (plus 2 m for acceleration and 2 m for deceleration) by using a stop watch
[32]. At the start and the finish there will be a standard chair with arm rests positioned. All walks will be performed barefoot. The participants will be instructed to walk at their comfortable normal walking speed
[33]. Time is recorded with a stop watch when the participant’s limb crosses the first marker until the participant’s limb crosses the second marker. During the second walk, participants will be asked to count backwards by three starting from a random 3-digit number (dual-tasking)
[34]. The potential resulting dual task interference will give an indication of the extent to which older people slow down when simultaneously walking and counting
[35].

A hydraulic hand grip dynamometer (Europe: Jamar Dynamometer, Lafayette Instrument, Lafayette, IN, USA; Australia: North Coast Hydraulic Hand Dynamometer, North Coast Medical, Inc., Morgan Hill, CA, USA) will be used to assess hand grip muscle strength. Participants will sit in a comfortable chair with the elbow flexed to 90 degrees, the wrist in a neutral position, and the shoulder adducted and neutrally rotated. After the participant exerts maximal force, strength is recorded to the nearest 1 kg. Each participant has three attempts while the highest score is used for analysis. Low muscle strength will be classified as hand grip strength <30 kg in men and <20 kg in women according to the European Working Group on Sarcopenia in Older People consensus paper
[31].

To assess the participants’ level of physical activity, the Incidental and Planned Activity Questionnaire (IPEQ)
[36] will be used in the Australian and Spanish study arm. The IPEQ consists of a self-report questionnaire which focusses on the frequency and duration of several levels of planned and incidental physical activity in older people. This questionnaire focuses on weekly physical activity including planned exercises or walks, and more casual day-to-day activities. The total duration of physical activity is summed across all components and expressed as hours per week. Measurement properties and concurrent validity for the IPEQ have been reported to be excellent
[36]. In the German study arm the Physical Activity Questionnaire for the population aged 50 years and older (PAQ-50+)
[37] will be applied. It evaluates physical activity during an average week of the past month. This questionnaire estimates physical activity of older people based on exercise, housework, gardening, job, and leisure activities. By multiplying the metabolic equivalent of an activity by the duration of performing the physical activity an estimate of total energy expenditure can be obtained. The PAQ-50+ showed an acceptable test-retest reliability of 0.52 to 0.60
[37].

#### Sensor-based physical assessments

Four sensor-based physical assessments using the iStoppFalls software, the Microsoft Kinect, and the SMM will be performed barefoot in front of a TV: (1) Balance tests include comfortable-bipedal, semi-tandem, near-tandem, and tandem stance (Figure 
5). Each balance task will be repeated twice for a maximum duration of 30 s with the preferred foot in front (no changes allowed between the different stances) and eyes open. After the countdown ‘ready, set, go’, time will be stopped when the participant moves his/her feet, touches the chair for support, or successfully reaches 30 s. (2) The hand reaction time test will require participants to use their hands to hit two randomly flashing lights positioned to the left and right on a virtual table. Two sets of 20 repetitions will be performed. (3) For the stepping reaction time test, two randomly flashing lights will be positioned to the left and right on a virtual floor. Participants will need to perform a lateral step onto the flashing light as fast as possible. Stepping should include weight-shifting rather than only foot tapping to the side. Two sets of 20 repetitions will be performed. (4) The sit-to-stand test is a functional measure for lower extremity strength, power, and balance. Participants will be instructed to cross their arms over the abdomen, and rise from a chair for five times as quickly as possible. Time measured by a stop watch indicates insufficient (≥16.7 s), sufficient (13.7 s to 16.6 s), good (11.2 s to 13.6 s), and very good strength performance (≤11.1 s)
[38].

**Figure 5 F5:**
[figure not shown]
**Base of support during static balance sensor-based assessments. (A)** bipedal stance, **(B)** near-tandem stance, **(C)** semi-tandem stance, **(D)** tandem stance. Picture by courtesy of bfu - Swiss Council for Accident Prevention.

### User activity and adherence

Based on the real-time user activity tracking inside the exergame (biomechanical model of the Kinect sensor) and overall iStoppFalls system (SMM and all human computer interactions), this study will be able to measure adherence to the protocol and correlate these results with the assessment outcomes. This will include the datasets of all exercises for each participant including complete biomechanical analysis of the range of motion as well as the quality of exercises performed in the balance games and strength training.

#### Neuropsychological assessments

The Mini-Cog will be used as a screening tool for cognitive impairment which forms part of the exclusion criteria
[12]. It consists of a 3-item recall and a clock drawing test (CDT). Participants recalling none of the words will be classified as cognitively impaired, those recalling all three words will be classified as cognitively healthy, and those with intermediate word recall (1 to 2) will be classified based on the CDT (abnormal = impaired, normal = healthy). For reasons of copyright protection, approval for the use of the Mini-Cog has been obtained by [name].

The Addenbrooke’s Cognitive Examination III (ACE-III) is a brief cognitive assessment including five domains: attention, memory, verbal fluency, language, and visuospatial abilities (
http://www.neura.edu.au/frontier/research/test-downloads/). The total score is 100 with higher scores indicating better cognitive functioning. The ACE-III replaces the previous Addenbrooke’s Cognitive Examination-Revised (ACE-R) showing high sensitivity and specificity at cut-offs previously recommended: 88 (sensitivity = 1.0; specificity = 0.96) and 82 (sensitivity = 0.93; specificity = 1.0)
[39]. Internal reliability using Cronbach’s alpha was good for the ACE-III (0.88)
[39].

The Trail Making Test (TMT) serves as a measure of executive function (divided attention), processing/motor speed, and mental flexibility
[40,41]. The participants will be asked to connect 25 encircled numbers (Part A) randomly arranged on an A4-sized paper in the correct order by using a pencil. In Part B, the participants will have to draw lines alternating between a total of 25 numbers and letters. For each part there will be a practice trial consisting of eight circles. The TMT is scored by measuring the time for the completion of each part, and by calculating ratio [Part B / Part A] and difference [Part B – Part A] scores
[42].

Cognitive control will be assessed by the Victoria Stroop Test (VST)
[41]. Participants will have to maintain a goal in mind and supress habitual responses to correctly perform the task. The VST consists of 24 items on each of three tasks: (1) identifying the colour of dots displayed in blue, green, red, or yellow; (2) identifying the colour of common words and disregarding their verbal content; and (3) identifying the ink colour of displayed colour words (e.g., ‘blue’ is written in red ink). A PC using the Psychology Experiment Building Language (PEBL) software version 0.13 in combination with a custom-made button device will be applied to perform the VST. The number of errors and time taken for each task will be recorded and stored locally on a PC.

The Digit Symbol Coding Test (DSC) is a multifaceted task (i.e., motor speed and incidental learning) from the Wechsler Adult Intelligence Scale (WAIS) III and will be used to investigate processing speed
[43]. It consists of nine symbols that are paired with numbers. Participants will be required to copy as many symbols as possible within 120 s. The primary measure of this test is the number of correct symbols.

The Digit Span Backward (DSB) from the WAIS-III is a measure of working memory, attention, and concentration
[43]. Participants will be required to repeat 2- to 9-digit numbers in the reverse order as stated by the investigator
[41]. Every task consists of two sets of numbers. If the participant fails to repeat both sets of numbers, the test will be terminated. Each correctly repeated set of numbers will be scored with one point.

The Attention Network Test (ANT) will be used to quantify the processing efficiency within three attentional networks: alerting, orienting, and executive attention
[44]. In this study a computer-based version of the ANT will be applied (PEBL software version 0.13)
[45]. The ANT requires participants to determine whether a central arrow points to the left or right. Efficiency of the three attentional networks (alerting, orienting, and executive function) is assessed by measuring how response times are influenced by alerting cues, spatial cues, and flankers. All data will be recorded and stored locally on a PC.

A single task measure of counting backwards by three will have to be obtained to measure the amount of interference caused by simultaneously walking and counting backwards by three (dual-tasking)
[35]. In this single task, participants will sit in a chair and start counting backwards by three from a random 3-digit number. The time stopped will be equal to the time used for the 10 m walk. To quantify interference, ratios between the correct number of answers during single-tasking will be compared to the number of correct answers during dual-tasking (dual task costs = [100 * (single task score – dual task score)/single task score]
[46]. If the participant continues to count correctly after making a mistake, this will only be counted as one mistake.

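### The seated counting-backwards score is a raw count over the participant's own 10 m walk time, so it falls as walking gets faster, and the plan does not say which of the two walks sets that time

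*Protocol article*

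**What the plan says.** All references are to Methods/Design of the protocol article.

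- **Physical and functional assessments.** The walk is timed over a set distance ("Steady-state walking speed will be measured over a 10 m distance") at a self-chosen pace ("The participants will be instructed to walk at their comfortable normal walking speed"). There are two walks: "During the second walk, participants will be asked to count backwards by three starting from a random 3-digit number". The section expects people to slow down in the second.
- **Neuropsychological assessments.** The seated single-task count serves to measure interference. Its duration rule is "The time stopped will be equal to the time used for the 10 m walk". The score is a count: "ratios between the correct number of answers during single-tasking will be compared to the number of correct answers during dual-tasking". The formula is "dual task costs = [100 * (single task score – dual task score)/single task score", which contains no time term.
- **Outcome measures, Table 1.** "Counting backwards by three" is a secondary outcome under Cognition at baseline and week 16. Walking speed, single and dual task, is a separate secondary outcome at the same visits. The table does not say whether the counting variable is the seated count or the dual-task cost.
- **Statistical analyses and sample size.** Treatment effects at follow-up are estimated by ANCOVA adjusted for the baseline value.

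The Discussion names gait velocity and cognition among the effects the trial will examine.

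**The concern.** The length of the seated test is set by walking time, which the programme may change. A participant who walks faster at week 16 than at baseline gets less time to count and is expected to score lower. ANCOVA on the baseline score does not remove this, because the window itself has changed between visits. If gait improves in one arm only, part of the arm difference in the seated count comes from the scoring rule. By contrast, the Digit Symbol Coding test in the same section counts correct symbols within a fixed 120 s.

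The second problem is the unnamed walk. The cost formula compares two counts, which is fair only if both were collected over the same length of time. Whether they were depends on which walk is meant. Three sites administer the test, and the sentence leaves room for them to do it differently.

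**Working it through.** The plan states no figure on this point, so there is nothing to reproduce. The check is algebra on the stated rule.

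**Inputs from the article:** distance 10 m; window equal to a 10 m walk time; score equal to correct answers; the cost formula above.

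**Assumptions, not in the article:** seated counting rate r of 0.5 correct answers/s (range 0.3 to 0.7); walking speeds of 0.9 to 1.3 m/s; dual-task slowing s of 0 to 30%; true loss of counting rate while walking c of 20% or 0%.

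**1. Seated count.** Expected score S = r × T, with T = 10/v.
- At r = 0.5: 0.9 m/s gives 11.1 s and 5.56 answers; 1.0 gives 5.00; 1.1 gives 4.55; 1.2 gives 8.33 s and 4.17; 1.3 gives 7.7 s and 3.85.
- A 10% faster walk multiplies S by 1/1.1 = 0.909, a fall of 9.1%. For example, 1.2 to 1.32 m/s shortens the window from 8.33 to 7.58 s and lowers the count from 4.17 to 3.79.
- A 20% faster walk multiplies S by 1/1.2 = 0.833, a fall of 16.7%.
- The percentages do not depend on r. Only the absolute counts do.

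**2. Dual-task cost, general form.** The dual-task count is D = r(1 − c) × T_dual, so

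cost = 100 × (S − D)/S = 100 × [1 − (1 − c) × T_dual/T_window].

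**3. Window set by the dual-task walk of the same visit.** T_dual/T_window = 1, so the cost from expected counts is 100c: 20% when c = 20%, at every speed.

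**4. Window set by the plain walk.** With slowing s, T_dual/T_window = 1/(1 − s). For c = 20%:

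| Dual-task slowing | Cost by the formula | True cost |
|---|---|---|
| 0% | 20.0% | 20% |
| 10% | 11.1% | 20% |
| 20% | 0% | 20% |
| 30% | -14.3% | 20% |

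**5. Direction of change over time under the plain-walk reading.** Take c = 0, so that cost = 100 × (1 − v_plain/v_dual), and start from 1.2 m/s plain and 1.0 m/s dual: cost = -20%.
- Dual-task walk alone rises to 1.1: 1 − 1.2/1.1 gives -9.1%, an apparent worsening of 11 points.
- Plain walk alone rises to 1.32: 1 − 1.32/1.0 gives -32%, an apparent improvement.
- Both rise by 10%: 1 − 1.32/1.1 gives -20%, no change.

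**6. Scored per second.** The rates are r and r(1 − c), so the cost is 100c under either reading and at any speed.

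**7. Zero seated score.** The formula is undefined at S = 0. If counts were Poisson, an 8.33 s window at 0.3 answers/s has mean 2.5 and P(0) = exp(−2.5) = 8.2%. At 0.6 answers/s the mean is 5.0 and P(0) = 0.7%. These figures rest on both the assumed rate and the Poisson model.

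**The case against.** The seated count is introduced as a comparator for the dual-task condition, and the dual-task cost is the only derived score the section defines. No sentence says that the raw seated count will be compared between arms. For the cost, matching the two durations is a sensible safeguard, and in context the walk done while counting is the natural reading. On that reading step 3 shows nothing wrong in expectation. Walk times are recorded, so a fuller protocol or analysis plan could still convert to rates. All this stands, and it makes the first part conditional on the seated count being analysed in its own right. It does not settle the matter: Table 1 lists the counting test as an outcome without saying which variable is meant, the walk is not named, and matched windows do nothing for a seated count analysed alone.

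A reader might go further and infer that the rule biases the counting results against the intervention throughout, so that the trial could report no cognitive benefit, or harm, as an artefact. The article does not support that. The adverse direction holds for the seated count when gait improves. For the cost under the plain-walk reading, step 5 shows that the sign depends on which walk changes. Six other secondary cognitive tests (ACE-III, Trail Making, Stroop, Digit Symbol Coding, Digit Span Backward, Attention Network) have no window tied to walking time.

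The zero-score percentages should not carry weight either. Serial subtraction is a paced task and may vary less than Poisson, and participants are screened for cognitive impairment.

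**Conclusion.** The point holds in a limited form. If the seated count is the Table 1 outcome, faster walking lowers it by the scoring rule alone: 9.1% fewer expected answers for a 10% faster walk, whatever the counting rate, provided that rate is steady over the window. The dual-task cost is sound in expectation if the dual-task walk of the same visit sets the window. If the plain walk does, the cost is understated, can turn negative, and moves over time in a direction that depends on which walk changes. The sizes in steps 4 and 5 rest on assumed slowing, speeds and interference; the understatement whenever the dual-task walk is slower does not. The matter is modest: it concerns one of several secondary cognitive outcomes and leaves the PPA and EQ-5D primary outcomes untouched. It is still worth correcting, because the repair is nearly free and right under either reading.

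**What to change.** 1. Define the score in both conditions as correct answers per second, and compute the dual-task cost from the two rates. State in Table 1 whether the outcome is the seated rate, the cost, or both.
2. State that the dual-task walk of the same visit sets the seated window, at all three sites.
3. Pre-specify one between-arm analysis for all participants that does not divide by the seated score, for example ANCOVA of the dual-task rate with the single-task rate as a covariate. Say at which visit that covariate is measured, since the week-16 value is itself obtained after randomisation. Do not switch method only for participants with a zero seated score; that would analyse one outcome in two ways according to its own data.

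The cost is a sentence or two in the outcome definition and one in the analysis section. No new measurement is needed: the walks are already timed, and the seated duration equals one of those times by rule. If testing has begun, each site should confirm which walk time it used so that the correct divisor is applied.
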